#### Trial Termination Criteria

Satisfaction of any of the following criteria will result in discontinuation of the clinical trial before the planned end in order to protect participants’ rights and ensure research quality:

Serious safety issues arising during the study requiring immediate termination.Major errors discovered in the clinical research protocol, making it difficult to evaluate drug efficacy; or important deviations occurring from a well-designed protocol, compromising the efficacy evaluation.Very favorable outcomes observed in the TCM group during the study warranting that the trial be terminated early to allow the control group to receive the TCM treatment.Termination requested by the research team (eg, due to funding or management issues).Termination required by administrative authorities.

#### Conditions and Procedures for Participant Withdrawal

There are two routes for participant withdrawal.

Withdrawal determined by the investigator: This may occur when a participant already enrolled in the study becomes unsuitable for continued participation due to the development of complications, comorbidities, or special physiological changes. Other conditions include poor compliance, defined as taking less than 80% or more than 120% of the prescribed medication, and the use of prohibited medications as per protocol.

Participant-initiated withdrawal: According to the informed consent form, participants have the right to withdraw at any time. If a participant stops taking the medication or attending visits without formally withdrawing, they are still considered “withdrawn” (or “lost to follow-up”). Reasons for withdrawal should be documented where possible and may include feeling the treatment is ineffective, the development of intolerable adverse reactions, personal circumstances, financial reasons, or unexplained loss to follow-up.

Regardless of the reason, case report forms for withdrawn participants should be retained. The last recorded test results will be used as final data, and both efficacy and adverse events will be analyzed in the full dataset.

### Intervention

Referring to the guidelines for clinical management of cerebrovascular diseases in China (second edition) [20], both groups will receive conventional rehabilitation training guidance, including assessment and rehabilitation of cognitive function, speech ability, swallowing function, limb motor and sensory function, balance, psychological state, and daily living abilities. They will also receive standard treatments such as antiplatelet therapy, lipid-lowering and blood pressure control, plaque stabilization, and electrolyte balance maintenance.

On the basis of conventional treatment, the study group will take Qizhi Jieyu pills, 9 g per dose, twice daily after meals. The control group will receive conventional treatment only. The intervention period is 12 weeks, with a total follow-up period of 48 weeks.

All TCM drugs with the same therapeutic effect as the investigational drug (including those with similar indications or efficacy stated in the instructions) are prohibited during the study. All concomitant medications and treatments (ie, for other diseases) must be recorded in the concomitant medication log.

### Study Procedures

Table 1 outlines the specific measurements and timepoints for data collection in this study. Eligible participants will undergo a 1-week preintervention screening period, a 12-week treatment period, and a total 48-week follow-up period. After the study begins, all enrolled participants will have follow-up visits every 12 weeks. All participants will be informed of the study through oral and written information and will be required to sign an informed consent form.

**Table 1 table1:** Clinical trial research timeline.

Item		Screening period and baseline	Visit 1	Visit 2	Visit 3	Visit 4
Visit time		–7 to 0 days	12 weeks ± 7 days	24 weeks ± 7 days	36 weeks ± 7 days	48 weeks ± 7 days
**Collect basic medical history**						
	Sign informed consent form	×				
	Fill in general information	×				
	Medical history and treatment history	×				
	Determine the inclusion and exclusion criteria	×				
	Vital signs	×	×	×	×	×
	Physical examination	×	×	×	×	×
	Merge diseases and medication	×	×	×	×	×
**Diagnosis and monitoring inspection**						
	Urine pregnancy test	×				
	Blood sugar, blood pressure, and blood lipids	×	×	×	×	×
	Brain CT^a^ or MRI^b^	×	×	×	×	×
**Effectiveness outcome**						
	NHISS^c^ score	×	×	×	×	×
	Recurrent cerebral infarction	×	×	×	×	×
	Traditional Chinese medicine symptom score	×	×	×	×	×
	Rankin Scale	×	×	×	×	×
**Physical and chemical examination**						
	Routine bloods, routine urine, and microscopic examination	×			×	×
	Routine stool	×			×	×
	Vital signs	×	×	×	×	×
	Electrocardiogram and liver and kidney function	×	×	×	×	×
	Adverse events		×	×	×	×

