**Other items**						
	Randomization	×				
	Distribute medication and patient diary cards	×	×	×	×	
	Recycling drugs and quantity statistics		×	×	×	×
	Retrieve patient diary cards		×	×	×	×
	Conclusion of the study					×

^a^CT: computed tomography.

^b^MRI: magnetic resonance imaging.

^c^NIHSS: National Institutes of Health Stroke Score.

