#### Safety Outcomes

Safety will be assessed using the following monitoring indicators:

Vital signs, including temperature, blood pressure, respiration rate, and heart rate, checked every 12 weeks.Routine tests, including blood, urine, and stool tests, every 12 weeks.Other labs and diagnostics, including electrocardiograms, liver function tests (alanine aminotransferase, aspartate aminotransferase, gamma-glutamyltransferase, alkaline phosphatase, and total bilirubin), and kidney function tests (blood urea nitrogen and creatine), every 12 weeks.Adverse events: From the time the participant enters the study until the final follow-up, adverse events will be monitored for 48 weeks. All information related to adverse events will be carefully recorded at all times. Serious adverse events refer to any unexpected clinical events occurring at any dose that result in hospitalization, prolongation of existing hospitalization, disability, impaired ability to work, life-threatening conditions or death, or congenital malformations. Serious adverse events will be reported to the study center and the principal medical ethics committee. In addition, they will be reported to the National Medical Products Administration within 24 hours. Meanwhile, we will specifically record adverse events potentially related to animal-derived components, such as itching, rash, allergic reactions, and gastrointestinal discomfort.

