## Results

The study was approved by the Ethics Committee of Guang’anmen Hospital, China Academy of Chinese Medical Sciences, on March 3, 2025 (2025-025-KY-01), and was registered on the International Traditional Medicine Clinical Trial Registry on April 6, 2025 (ITMCTR2025000653), and any potential protocol amendments will be recorded there. Participant screening began on April 10, 2025, with enrolment expected to be completed by December 31, 2025. The final study results are planned to be published by December 31, 2026.

This study aims to evaluate the efficacy and safety of Qizhi Jieyu pill in the treatment of patients in the recovery phase of cerebral infarction, providing a treatment option supported by high-quality, evidence-based medicine for the clinical management of recovery phase cerebral infarction.

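### Table 1 omits the week-12 and week-24 routine blood, urine and stool tests that the safety text requires, so no post-baseline result is scheduled before week 36

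*Protocol article*

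**What the plan says.** The Safety Outcomes section of the protocol article lists, among its monitoring indicators, "Routine tests, including blood, urine, and stool tests, every 12 weeks". Study Procedures fixes the visit spacing: "all enrolled participants will have follow-up visits every 12 weeks". Table 1 places those visits at weeks 12, 24, 36 and 48, each ± 7 days.

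In the physical and chemical examination block of Table 1, the rows "Routine bloods, routine urine, and microscopic examination" and "Routine stool" carry marks at baseline, visit 3 (week 36) and visit 4 (week 48). Visits 1 and 2 are blank in both. In the same block, "Electrocardiogram and liver and kidney function" and vital signs are marked in all five columns.

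Two further statements govern how a week-36 result would be read. The Intervention section says "The intervention period is 12 weeks, with a total follow-up period of 48 weeks". Table 1, however, marks the row "Distribute medication and patient diary cards" at baseline and at weeks 12, 24 and 36.

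**The concern.** The article gives the schedule for the same tests twice, and the two versions differ. This is a contradiction, not a detail left out of a condensed article.

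It matters because safety is half of the stated objective. The pill has 26 herbal and animal-derived components, is added to standard treatment that includes antiplatelet therapy, and by the authors' own account lacks high-quality safety evidence. Blood counts, urinalysis and stool examination can show changes that produce no symptoms and so would not surface as reported adverse events. If Table 1 is what sites follow, those changes have no scheduled measurement while a 12-week course is being taken or at its end.

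**Working it through.** No formula or stated figure is involved. The check sets the text against the table and then counts weeks.

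**1. Schedule side by side** (Safety Outcomes; Study Procedures, Table 1)

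| Source | Baseline | Wk 12 | Wk 24 | Wk 36 | Wk 48 |
|---|---|---|---|---|---|
| Safety Outcomes text, 12-weekly | not stated | yes | yes | yes | yes |
| Table 1, routine blood and urine | × | – | – | × | × |
| Table 1, routine stool | × | – | – | × | × |
| Table 1, ECG, liver and kidney function | × | × | × | × | × |
| Table 1, adverse events | – | × | × | × | × |

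Post-baseline assessments per test: 4 in the text, 2 in the table. Missing marks: 2 rows × 2 visits = 4.

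**2. Is this a table-reading error?** Unlikely. Both affected rows show the same pattern of mark, blank, blank, mark, mark. The neighbouring rows line up with the five visit columns, and the adverse events row is blank only at baseline, as expected.

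**3. Which version is intended?** The section on clinical materials and samples, under Data Collection and Management, has blood, urine and stool samples stored after each follow-up. That agrees with the 12-weekly text. Apart from the two rows at issue, the only urine test in Table 1 is the baseline pregnancy test, and stool appears nowhere else. Table 1 is therefore the outlier.

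**4. Timing of the first post-baseline result if Table 1 is followed**

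- *12-week course (Intervention section):* 36 − 12 = 24 weeks after the end of the course. With the ± 7 day window at visit 3, this runs from 35 − 12 = 23 to 37 − 12 = 25 weeks.
- *Dosing according to the medication row (dispensing at weeks 0, 12, 24 and 36):* the first result comes after up to 36 weeks of dosing.

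The first 12 weeks of treatment are uncovered under both readings.

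**5. Can the gap still be closed?** The Results section states: "Participant screening began on April 10, 2025, with enrolment expected to be completed by December 31, 2025".

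- Earliest nominal week-12 visit: April 10, 2025 + 84 days = July 3, 2025. This assumes that the first person screened had baseline that day. It falls before the article's publication on August 13, 2025.
- Nominal week-12 visit of a participant enrolled on December 31, 2025: + 84 days = March 25, 2026.

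Some week-12 tests may already have been missed at publication, while those of later enrollees still lay ahead.

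**The case against.** The strongest reply accepts the mismatch and disputes its weight.

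- **Scope.** The primary outcome, sample size and efficacy analyses are untouched. Liver and kidney function, ECG, vital signs, adverse events, blood sugar and lipids are all scheduled at every post-baseline visit. This stands, and it limits the point to three routine tests.
- **Conditional harm.** Sites normally work from the full protocol and case report form, not from a journal table, and the text already shows what was intended. This stands in part: the contradiction is certain, its effect on conduct is not. Unscheduled tests also remain possible, so the gap is one of scheduled results.
- **Only one visit matters.** Under a 12-week course, week 24 is already 12 weeks after treatment, so only the week-12 cells lose an on-treatment or end-of-treatment result. That is right under this reading. Under the medication row, both visits fall within dosing. The text promises both in either case.
- **The dosing conflict is a separate matter.** It is not needed to establish the mismatch. It does decide how a week-36 value is interpreted, so settling it in the same correction is sensible.
- **The dates are approximate.** With the ± 7 day window, the earliest week-12 visit could fall about June 26, 2025. This does not change the conclusion that later enrollees can still be tested.

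None of this reconciles the two schedules. A slip that decides whether safety samples are taken is more than clerical.

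**Conclusion.** The concern holds. Table 1 contradicts the Safety Outcomes text on routine blood, urine and stool tests, and the table is the version to correct. If it is followed, half of the stated post-baseline assessments (weeks 12 and 24) are lost for these tests, and nothing is scheduled during or at the end of a 12-week course.

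Confidence in the contradiction is high. The practical consequence rests on the assumption that sites follow Table 1, which the article does not settle. The point should be corrected. It bears on the completeness of safety data, not on the efficacy conclusion.

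**What to change.** - Add marks at visits 1 and 2 (weeks 12 and 24) to both Table 1 rows. Do not cut the text back to match the table: that would remove the only scheduled routine blood, urine and stool tests within or at the end of a 12-week course.
- Check which schedule the full protocol and case report form carry, and notify both sites promptly.
- In the same correction, state whether the 12-week intervention or the medication distribution row governs dosing. The week-12 mark is needed under either answer.
- Where week-12 or week-24 tests were already missed, report the number tested by arm and visit. If the course is 12 weeks, draw no on-treatment safety conclusion about these tests from those participants' later values.

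The cost is four marks and one site memo. There are no new visits, since visits 1 and 2 already include liver and kidney function tests, and no tests beyond those the text already commits to. Tests already missed cannot be recovered.

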**Other items**						
	Randomization	×				
	Distribute medication and patient diary cards	×	×	×	×	
	Recycling drugs and quantity statistics		×	×	×	×
	Retrieve patient diary cards		×	×	×	×
	Conclusion of the study					×

^a^CT: computed tomography.

^b^MRI: magnetic resonance imaging.

^c^NIHSS: National Institutes of Health Stroke Score.

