**Methods:**

This study adopts a multicenter, randomized controlled clinical trial design. A total of 126 patients aged 30-70 years in the recovery phase of cerebral infarction will be recruited and randomly assigned in a 1:1 ratio to either the study group (n=63, receiving conventional treatment plus Qizhi Jieyu pill) or the control group (n=63, receiving conventional treatment alone). The intervention period will last 12 weeks, and the total follow-up period will be 48 weeks. The primary outcome is the change in the National Institutes of Health Stroke Scale score at week 48. Secondary outcomes include changes in traditional Chinese medicine syndrome scores, the recurrence rate of cerebral infarction, and modified Rankin Scale scores. Adverse events will be recorded and used to assess the safety profile. All data analyses will be performed according to a prespecified statistical analysis plan.

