**Figure 1 figure1:**
[figure not shown]
Study flowchart illustrating the trial design, including the screening of 126 eligible participants with cerebral infarction in the recovery phase, randomization into 2 groups (Qizhi Jieyu pill plus conventional treatment versus conventional treatment alone), a 12-week treatment period, and follow-up assessments at weeks 12, 24, 36, and 48. The outcomes assessed include changes in National Institutes of Health Stroke Scale (NIHSS) scores, traditional Chinese medicine (TCM) symptom scores, recurrence rates, Rankin Scale scores, and adverse events.

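### Table 1 schedules drug dispensing and return over 48 weeks, while the text states a 12-week treatment period

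*Protocol article*

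**What the plan says.** Four places in the protocol article give the length of treatment, and they agree:

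- Abstract, Methods: "The intervention period will last 12 weeks, and the total follow-up period will be 48 weeks".
- Intervention: "The intervention period is 12 weeks, with a total follow-up period of 48 weeks".
- Study Procedures: "a 12-week treatment period, and a total 48-week follow-up period".
- Figure 1 caption: "a 12-week treatment period, and follow-up assessments at weeks 12, 24, 36, and 48".

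Study Procedures adds that "all enrolled participants will have follow-up visits every 12 weeks". The header of Table 1 places Visits 1 to 4 at weeks 12, 24, 36 and 48.

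Under Other items, Table 1 gives a different picture of drug handling. The row "Distribute medication and patient diary cards" is marked at baseline and at weeks 12, 24 and 36, and is blank at week 48. The row "Recycling drugs and quantity statistics" is blank at baseline and marked at weeks 12, 24, 36 and 48. Retrieval of diary cards has its own row. No footnote or text explains why drug is handled after week 12.

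**The concern.** A 12-week course with visits every 12 weeks needs drug handed out at baseline and leftovers counted at week 12. Table 1 repeats that cycle to the last visit. A reader of the text and a reader of the schedule would therefore reach different conclusions about how long the study group takes the pill.

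Four parts of the plan depend on the answer:

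- **Primary outcome.** The change in NIHSS score is taken at week 48. Whether this reflects the end of continuous treatment or persistence after a long period off treatment is a different scientific question.
- **Compliance.** The section on participant withdrawal defines poor compliance as "taking less than 80% or more than 120% of the prescribed medication". The amount prescribed follows from the treatment length.
- **Case elimination.** One criterion removes cases whose exposure fell short of what the trial requires, so the required exposure must be known.
- **Per protocol set.** Membership requires the participant to have finished treatment.

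**Working it through.** The plan gives no figure for total exposure to reproduce, so the check sets the schedule against the text and then sizes the gap.

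**Inputs**
- Treatment period in the text: 12 weeks (abstract, Figure 1 caption, Intervention, Study Procedures).
- Dispensing visits in Table 1: weeks 0, 12, 24, 36.
- Return-and-count visits in Table 1: weeks 12, 24, 36, 48.
- Frequency: two doses a day (Intervention).
- Compliance band: 80% to 120% of the prescribed amount (participant withdrawal section).
- Primary outcome time: week 48 (Primary Outcome).

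**Step 1. Dosing period implied by Table 1.** Pair each dispensing visit with the next return visit: 0–12, 12–24, 24–36, 36–48. Total = 4 × 12 = 48 weeks. The text implies only the first pair.

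**Step 2. Could the marks be misread?** The dispensing row combines drug and diary cards, so taken alone its later marks could mean cards only. The drug return and count row is separate from the diary-card retrieval row, and it is marked at weeks 24, 36 and 48. It therefore does not allow a cards-only reading. A text-extraction fault is unlikely: the dispensing row is blank only at the last visit and the return row only at baseline, which is a coherent dispense-then-return pattern across the five columns.

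**Step 3. Potential exposure.** Doses = weeks × 7 × 2.

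| | 12 weeks (text) | 48 weeks (Table 1 pattern) |
|---|---|---|
| Doses | 12 × 7 × 2 = 168 | 48 × 7 × 2 = 672 |
| 80% limit | 0.8 × 168 = 134.4 | 0.8 × 672 = 537.6 |
| 120% limit | 1.2 × 168 = 201.6 | 1.2 × 672 = 806.4 |
| Week 48 relative to end of treatment | 48 − 12 = 36 weeks after | 48 − 48 = 0 |

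The ratio of exposures is 672 / 168 = 4. The two compliance bands do not overlap.

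**Step 4. Cross-scoring.** If intake on one schedule were judged against the other, full adherence would score 168 / 672 = 25% or 672 / 168 = 400%. Judged against its own schedule, each scores 100%.

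**The case against.** The strongest reply is that four statements, including the section that governs treatment, agree on 12 weeks, and that two rows of a schedule table are a drafting slip. Table 1 is loose elsewhere: Safety Outcomes calls for blood, urine and stool tests every 12 weeks, while Table 1 marks them only at baseline and weeks 36 and 48. The drug rows also neither name the pill nor restrict themselves to one arm. A slip is plausible, but the documents do not prove one, and nothing in them tells the reader which statement prevails. What stands of this reply is that exposure is not undefined. It is stated in two incompatible ways.

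Four stronger readings are tempting and are not supported:

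- **Participants would be withdrawn for scoring 25% or 400%.** Those figures arise only when one schedule is scored against the other. The withdrawal section also says that investigator-determined withdrawal may occur, not that it must.
- **The two centres are running different trials.** This is possible but not shown. The plan provides for standard operating procedures, unified training and on-site monitoring, and nothing shows that sites dispense from the article's table. These controls do not remove the contradiction.
- **Safety follow-up is affected.** The plan defines no on-treatment adverse event window. Adverse events are monitored for 48 weeks whatever the dosing period.
- **The primary analysis set is affected.** The full analysis set needs only randomization and one postbaseline efficacy evaluation. The condition of finishing treatment applies to the secondary, per protocol set.

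Leaving the matter to a statistical analysis plan or a fuller protocol is no answer here, because this is not an omission. The article states two things that cannot both hold.

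**Conclusion.** The point holds as an internal inconsistency. The text gives a 12-week treatment period, and the dispensing and return rows of Table 1 follow a 48-week pattern. Potential exposure differs fourfold, 168 against 672 doses. The base for the compliance rule, the exposure criterion for case elimination and the per protocol completion condition are ambiguous as a result. The time of the primary outcome is fixed, but its meaning is not: it is either an end-of-treatment effect or an effect 36 weeks after treatment ends.

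This rests on two assumptions: that the drug rows in Table 1 refer to the study pill, and that each dispensing visit supplies the interval to the next visit. The dose counts use the stated twice-daily regimen with no missed doses. The matter needs settling promptly, because recruitment began on April 10, 2025. Which period is correct is not for this review to say.

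**What to change.** Reconcile the two drug rows of Table 1 with the abstract, the Figure 1 caption, the Intervention section and Study Procedures, so that all state one dosing period. If any later mark concerns diary cards only, give the cards their own row. Then:

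- check the dispensing records at both sites against the reconciled period;
- state the compliance denominator, the exposure required to avoid case elimination, and the per protocol completion criterion in terms of that period;
- say explicitly whether the week-48 primary outcome is measured on or off treatment.

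The cost is a correction to the table or text, a memo to two sites and a review of existing dispensing records. No new participant assessments are needed.
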